#### Secondary outcomes

Secondary outcomes consist mainly of 16 indicators. It includes clinical and prognostic indicators (key secondary outcomes) and biochemical indicators (exploratory outcomes).

Clinical indicators include the following: (1) Average classification of the AGI grade, (2) gastric retention volume within 1 day, (3) abdominal circumference, (4) abdominal pressure, (5) frequency of bowel sounds, (6) number of days tolerating the daily feeding target, (7) proportion of patients receiving erythromycin and/or metoclopramide for feeding intolerance management, and (8) proportion of patients receiving one or more rectal laxatives for constipation management.

Biochemical indicators include the following: (1) Plasma concentration of motilin, (2) plasma concentration of gastrin, and (3) plasma concentration of prealbumin.

Prognostic indicators include the following: (1) Incidence of S-persistent inflammation, immunosuppression, and catabolism syndrome (PICS), (2) duration of invasive mechanical ventilation in days, (3) ICU length of stay in days, (4) mortality rate at day 7, and (5) mortality rate at day 28.

To assess gastrointestinal function, the AGI grade will be used (4). The AGI grade is widely used to evaluate gastrointestinal injury in patients with acute critical illness (4, 18). Evidence has shown that the AGI grading system is useful for determining the severity of gastrointestinal dysfunction/failure in sepsis (19). The specific criteria for AGI grading are provided in Supplementary File S1.

At baseline and on days 4, 8, and 10, AGI grading will be assessed, and gastric retention volume, abdominal circumference, abdominal pressure, and frequency of abdominal bowel sounds will be measured. The specific measurement procedures for these clinical indicators are detailed in Supplementary File S1. We will also record the gastric retention volume over the previous 24 h, the actual caloric intake from enteral nutrition, and any special treatments related to S-AGI, including the use of erythromycin and/or metoclopramide for feeding intolerance management or the use of one or more rectal laxatives for constipation management. In addition, we will collect venous blood samples from patients at baseline and on days 4, 8, and 10 to measure the plasma concentration of motilin and gastrin, which serve as indicators of gastrointestinal motility.

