### Sample size

A parallel-design, randomized controlled trial methodology will be employed in the trial, with the primary outcome measure being the incidence of S-AGI. Based on clinical observations, the estimated incidence of S-AGI in the conventional treatment group is 70%. It is anticipated that electroacupuncture can potentially reduce the occurrence rate of S-AGI to 50%. With a significance level (*α*) of 0.05 and a power of 0.8, the sample size calculation yielded 94 participants per group. To account for potential loss to follow-up, we plan to include a total of 200 sepsis patients, with 100 patients allocated to each group. To account for uncertainties and maintain adequate power if the effect size is smaller than expected, sample sizes were also calculated as 163 participants per group for a 15% effect size and 356 participants per group for a 10% effect size.

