### Statistical analysis

Statistical analysis will be performed using the SPSS software (version 29.0). For continuous data, a normality test will initially be conducted to assess distribution characteristics. If the data exhibit a normal distribution, descriptive statistics such as mean ± standard deviation (*SD*) will be used, and hypothesis testing will be carried out using a *t*-test. Conversely, if the data do not follow a normal distribution, descriptive statistics such as median and interquartile range (*IQR*) will be employed, and hypothesis testing will be performed using the *Mann–Whitney U* test. Categorical data will be described in terms of frequencies and percentages, with the chi-squared test used for hypothesis testing. The significance level for this study will be set at *α* = 0.05, with statistical significance defined as a *p*-value of <0.05. This trial includes 13 key secondary outcome indicators, covering both clinical and prognostic measures. To address multiplicity and control type I error, we applied the *Bonferroni* correction at both levels.

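### Holm's step-down procedure would be a cheap, optional improvement on the valid plain Bonferroni correction planned for the 13 key secondary outcomes

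*Protocol article*

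**What the plan says.** The Statistical analysis section sets the overall level: "The significance level for this study will be set at *α* = 0.05". It then counts the outcomes that need a correction: "This trial includes 13 key secondary outcome indicators, covering both clinical and prognostic measures". The purpose and the method follow: "To address multiplicity and control type I error", "we applied the *Bonferroni* correction at both levels".

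The Secondary outcomes section shows where the 13 comes from: "It includes clinical and prognostic indicators (key secondary outcomes) and biochemical indicators (exploratory outcomes"). It lists 8 clinical and 5 prognostic indicators, and 8 + 5 = 13, so the count is consistent. The 3 biochemical indicators are exploratory and lie outside the correction.

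The article gives no divisor and no corrected threshold. It does not say whether both levels means one family of 13, or the clinical and prognostic groups corrected separately. The Sample size section powers the primary outcome only; no power target is set for any secondary outcome.

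**The concern.** The article names a particular method here, so the choice can be assessed as it stands. Under plain Bonferroni every outcome in a family of m is held to 0.05/m, however many of the others have already been rejected. Holm starts at the same threshold and relaxes it after each rejection, with the same guarantee on family-wise error. On error control alone, Bonferroni offers nothing that Holm does not.

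The question is relevant to this trial because several key secondary outcomes describe the same domain: AGI grade, gastric retention, abdominal pressure, bowel sounds, feeding tolerance and prokinetic use. The article also links gut protection to time on the ventilator. If electroacupuncture works as the rationale supposes, several of these outcomes may move together, and that is where Holm gains most. At stake is whether some real secondary effects miss a significance threshold that an equally strict rule would have let them pass.

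**Working it through.** **Inputs from the article.** Alpha 0.05; 13 key secondary outcomes (8 + 5); Bonferroni; 100 patients per group; primary outcome 70% against 50%, power 0.8.

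**The plan's own figure first.** Two-sided test of two proportions, pooled variance under the null, no continuity correction:

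n = [1.96·√(2·0.6·0.4) + 0.8416·√(0.7·0.3 + 0.5·0.5)]² / 0.2² = (1.3579 + 0.5708)² / 0.04 ≈ 93 per group.

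The article says "a power of 0.8, the sample size calculation yielded 94 participants per group", which agrees to within one patient. The same formula gives 163 and 356 for the 15-point and 10-point differences, exactly as stated. So alpha is two-sided, and the calculation concerns the primary outcome alone.

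**Thresholds, one family of 13.**
- Bonferroni: 0.05/13 = 0.00385 for every outcome. Family-wise error under independence is 1 − (1 − 0.00385)¹³ = 4.89%, and at most 5% under any dependence. Without correction it would be 1 − 0.95¹³ = 48.7%.
- Holm, smallest p-value first: 0.00385, 0.00417, 0.00455, 0.00500, 0.00556, 0.00625, 0.00714, 0.00833, 0.0100, 0.0125, 0.0167, 0.025, 0.05, stopping at the first that is not met.

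No Holm threshold is below 0.00385, so Holm rejects everything that Bonferroni rejects. The first threshold is identical, so if Bonferroni rejects nothing, Holm rejects nothing either.

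**Bonferroni power by formula.** An effect with 80% power at an unadjusted two-sided 0.05 has mean z = 1.960 + 0.842 = 2.802. The critical z for 0.00385 is 2.891. Power is Φ(2.802 − 2.891) = Φ(−0.089) = 46.5%, which the simulation gives as about 46%. With 90% unadjusted power it is Φ(3.242 − 2.891) = 63.7%; with 50% it is Φ(1.960 − 2.891) = 17.6%.

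**Holm power by simulation.** 200,000 draws of 13 normal test statistics, pairwise correlation 0.3. Effect sizes and correlation are assumptions.

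| Unadjusted power of each real effect | Bonferroni | Holm, 4 real | Holm, 8 real | Holm, 13 real |
|---|---|---|---|---|
| 80% | 46% | 48% | 51% | 57% |
| 90% | 64% | 66% | 69% | 77% |
| 50% | 17.6% | +0.5 points | +1.4 points | +3.2 points |

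With 80% unadjusted power, Holm rejects at least one outcome more than Bonferroni in about 7% of trials when 4 effects are real and 28% when 8 are. Results at correlation 0 and 0.5 are similar.

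**Error control.** With 8 real effects at 90% unadjusted power, the chance of any false rejection among the other 5 is 1.9% with Bonferroni and about 3.4% with Holm, both under 5%.

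**If the two groups are corrected separately** (80% unadjusted power, correlation 0.3):
- Family of 8, Bonferroni threshold 0.05/8 = 0.00625: power 53%, against 56% with Holm when 4 are real and 64% when all 8 are.
- Family of 5, Bonferroni threshold 0.05/5 = 0.01: power 59%, against 63% with Holm when 3 are real and about 69% when all 5 are.

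The direction is the same on either reading of both levels.

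**The case against.** The strongest reply is that this is a preference between two valid methods. The stated aim is to control type I error, and Bonferroni does so under any dependence. No figure is wrong, no error rate is inflated and no power target is missed, because none exists for the secondary outcomes. All of that stands, and it limits the point to an optional improvement.

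A reader might infer that the plan gives up power for nothing. The documents do not support that. Bonferroni gives one fixed threshold per outcome and simultaneous intervals that agree with the tests; Holm has no equally simple intervals. The Statistical analysis section plans no such intervals, so the advantage is small here, but it is real.

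A reader might also infer that real effects on gastric retention, abdominal pressure or ventilation days would routinely be lost. The figures do not support that either. The gains of 11 to 13 points need all 13 effects to be real with 80% to 90% unadjusted power each. The 13 include mortality at days 7 and 28, and the Introduction itself describes the earlier mortality findings as inconsistent. With 4 to 8 real effects the gain is between about 0.5 and 5 points.

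Finally, the undefined phrase both levels is arguably the larger weakness in the sentence. Separate correction by group would allow family-wise error over all 13 of 1 − (1 − 0.00625)⁸(1 − 0.01)⁵ = 9.6% under independence, and up to 10% in general. That is a separate question. It does not rebut this one, but the fix has to respect it: imposing m = 13 on a plan that meant two families would lower the entry threshold from 0.00625 or 0.01 to 0.00385 and could reject less than the present plan.

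**Conclusion.** The point holds as a low-cost, optional gain in efficiency. Within any given family, Holm never rejects fewer outcomes than Bonferroni and holds the same family-wise error; that needs no assumption. The size does: with 80% unadjusted power per real effect and correlation 0.3, power per real effect rises from 46% to 48%, 51% or 57% with 4, 8 or 13 real effects out of 13. With about 50% unadjusted power the gain is 0.5 to 3 points. The chance of declaring at least one key secondary outcome is unchanged. Bonferroni as planned is not an error, and the primary test and sample size are not touched.

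**What to change.** In the Statistical analysis section, state which family or families both levels refers to, and replace Bonferroni with Holm inside each. Suggested wording: *Within each family of m key secondary outcomes, the ordered p-values are compared with 0.05/m, 0.05/(m − 1), ..., 0.05, stopping at the first that is not met; Holm-adjusted p-values are reported.* Use m = 13 for one family, or m = 8 and m = 5 if the clinical and prognostic groups are corrected separately. Any 95% confidence intervals shown beside the adjusted p-values should be labelled unadjusted, since such an interval can exclude no effect while the adjusted p-value is not significant.

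The change should be fixed before the data are unblinded. It costs one sentence and a short calculation on p-values that the planned tests already give: no extra patients, data or software. The only loss is the simple matching simultaneous intervals.

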## Discussion

In our clinical research proposal, we focus on sepsis patients who require invasive mechanical ventilation. Invasive mechanical ventilation is common among sepsis patients admitted to the ICU, with studies indicating that approximately 21.38%–51.67% of sepsis cases necessitate this intervention (25, 26).

According to our clinical observations, several factors contribute to the increased susceptibility of mechanically ventilated sepsis patients to S-AGI. First, these individuals often exhibit a more severe clinical status, characterized by hypotension and multi-organ dysfunction that can compromise splanchnic blood flow and gastrointestinal integrity. Second, the use of sedatives and analgesics during mechanical ventilation can diminish gastrointestinal motility and impair the protective mucosal barrier, further predisposing patients to S-AGI. Moreover, the inflammatory response associated with sepsis can directly disrupt gut barrier function. A previous study reported that clinical ill patients who received preventive treatment for AGI exhibited a notably higher intake of the nutrient solution and a considerably shorter duration of invasive mechanical ventilation compared to those without any preventive measures (5).

S-AGI significantly impacts the prognosis of sepsis patients, increasing the risk of complications and mortality. Currently, there are no effective preventive strategies for S-AGI, underscoring the need for alternative interventions. Electroacupuncture has shown potential in preventing S-AGI; however, high-quality evidence from RCTs remains scarce. Therefore, it is crucial to conduct an RCT to establish the efficacy of electroacupuncture in preventing S-AGI, providing much-needed evidence to guide clinical practice and improve outcomes in sepsis patients.

In this clinical trial, we opt for an open-label design rather than using sham acupuncture as a control due to the lack of recognition and rigor associated with sham acupuncture methods. The current understanding in the field suggests that sham acupuncture does not adequately mimic the physiological effects of true acupuncture. Furthermore, sham acupuncture has several drawbacks, including the difficulty of effectively blinding both participants and clinicians. This can lead to biases in outcome reporting and subjective assessments, which can ultimately compromise the validity of the results (27–29). In addition, patients with sepsis requiring invasive mechanical ventilation usually require analgesia and sedation, remaining in a sedated state. Therefore, not using a sham acupuncture protocol in the control group will not affect outcome assessments. Consequently, we decided against employing sham acupuncture as a control in this RCT. Instead, the study will focus on evaluating the therapeutic effects of electroacupuncture compared to standard care, enabling a more direct assessment of its effectiveness in preventing S-AGI. This approach enhances the scientific credibility of the trial by minimizing bias and ensuring that the findings accurately reflect the intervention’s impact. By adopting an open-label design, our objective is to provide robust and dependable evidence that could inform clinical practices and improve treatment outcomes for sepsis patients at risk of AGI.

In open-label clinical studies, there is a high risk of selection, performance, and measurement bias. To minimize these biases, we will implement the following measures. First, to prevent selection bias, inclusion and exclusion criteria will be defined clearly to ensure baseline consistency among participants and reduce potential effects on outcomes. Randomization sequences will remain concealed until participants are confirmed eligible and enrolled. Second, to minimize performance bias, standardized intervention protocols and detailed manuals will be used in operations. Researchers will receive training from the project leader to ensure consistent implementation and assessment. Third, to mitigate measurement bias, outcome assessors and statisticians will be blinded to treatment assignments and data, respectively, until the analysis is complete. We will use an intention-to-treat approach to include data from all participants regardless of study completion, and we will report the reasons for, as well as the number of, missing data in each group.

This study will be the first large-sample randomized controlled trial to evaluate the efficacy of electroacupuncture in preventing S-AGI in patients with sepsis undergoing mechanical ventilation. We will assess the effects of electroacupuncture and compare the difference between the electroacupuncture and standard care groups in an adequately powered trial.
